#### 2.8.8. Tolerance and Adverse Events

Nausea, diarrhea, dysphagia, vomiting, constipation, and abdominal pain are gastrointestinal symptoms that are used to measure product consumption tolerance. However, they are also considered supportive indicators that can impair food intake or absorption, an etiological criterion used for malnutrition diagnosis [23]. Symptoms of intensity, frequency, and duration will be collected in a diary sheet throughout the study and evaluated at every visit, and the percentage change between visits will be compared between treatments. Gastrointestinal disorders will be judged using Common Terminology Criteria for Adverse Events (CTCAE) from the National Cancer Institute [82]. These adverse events will be used to discern the severity of food intake or absorption impairment and evaluate tolerance to the nutritional intervention. CTCAE will be evaluated at the beginning (v1) and end of the intervention (v5), and the percentage change between these two visits will be compared between treatments. Evolution will also be measured on v1, v3, v4, and v5.

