#### 3.4.7. Tolerance and Adverse Events

A diary sheet is given where the patient writes down the possible adverse events, symptoms presented, symptoms date (beginning and end), intensity (mild, moderate, intense), a possible relationship with the product (yes, no, it is possible) and behavior adopted. On every visit, the patient is also asked about any other discomforts not written down because they are considered light and related to product consumption. Gastrointestinal disorders such as abdominal distension, abdominal pain, nausea, regurgitation or gastroesophageal reflux, vomiting, constipation, diarrhea, and flatulence are defined and recorded based on Common Terminology Criteria for Adverse Events (CTCAE) from the National Cancer Institute [82]. These adverse events are classified as Grade 0 (not described), Grade 1 (mild), Grade 2 (moderate), Grade 3 (severe), Grade 4 (mortality risk), and Grade 5 (death associated with an event).

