## 5. General Characteristics of the Population

This section presents very preliminary results of the clinical trial. For the present study a total of 62 patients were evaluated for eligibility. Of them, 31 met the selection criteria and were randomized into three intervention groups (Figure 5). During follow-up, there were 10 dropouts, mainly due to the consumption of the supplement distorted the taste of some non-sweet acidic foods (n = 6) and because of the prescription added difficulty to their, already complex, antineoplastic treatment (n = 2). A final sample of 21 patients completed the clinical trial.

The sample was made up of 61.9% women and 38.1% men with a mean age of 59.8 ± 11.65 years old, all of them undergoing active treatment with chemotherapy and taste alteration measured by electrogustometry (Table 3). The average body mass index was 22.37 ± 3.67 kg/m^2^, classifying the patients as normal weight. However, the weight lost in the last 3 months was −7.60 ± 5.76%, with no significant differences between treatment groups. 

The most prevalent type of cancer was colorectal cancer (28.6%) followed by breast, lung, pancreas and liver cancers, each with 9.5%. Fasting glycemic control (105 ± 19 mg/dL) was within the normal reference parameters (74–106 mg/dL). The insulin concentration (12 ± 10 µU/mL) was normal in the entire population (3–25 µU/mL) as well as the lipid profile. All patients had systemic inflammation (CRP > 5 mg/dL). Both vitamins and minerals were found within the reference values except for vitamin D, which means blood concentration (21.25 ± 13.86 ng/mL) was insufficient (range 15–30 ng/mL).

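### The between-arm CTCAE comparison is a v1-to-v5 change that at most 21 of 31 patients can enter, and no on-treatment incidence, worst grade or product-related stopping is compared

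*Protocol article*

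**What the plan says.** Section 2.8.8 sets up two streams of tolerance data, each with its own between-arm comparison.

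- **Diary.** The intensity, frequency and duration of gastrointestinal symptoms "will be collected in a diary sheet throughout the study and evaluated at every visit". The comparison between arms is then set as follows: "the percentage change between visits will be compared between treatments".
- **CTCAE grades.** "CTCAE will be evaluated at the beginning (v1) and end of the intervention (v5), and the percentage change between these two visits" is compared between treatments. The next sentence adds: "Evolution will also be measured on v1, v3, v4, and v5".

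Section 3.4.7 gives the content. "A diary sheet is given where the patient writes down the possible adverse events, symptoms presented, symptoms date (beginning and end"), together with intensity and possible relation to the product. The CTCAE list is gastrointestinal, and its scale starts at zero: "These adverse events are classified as Grade 0 (not described), Grade 1 (mild"), rising to grade 5.

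Three other sections decide who has a v5 value. Section 2.1 makes inability to tolerate the tablets a withdrawal criterion. Section 2.5 ends participation when the prescribed dose is not followed. Section 2.12 keeps the patient's record but reduces the sample size of a variable to the values available. Section 2.2 has leavers asked whether an adverse event from the tablets was the reason, without naming an analysis of the answer.

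Section 5 reports that "there were 10 dropouts, mainly due to the consumption of the supplement distorted the taste of some non-sweet acidic foods (n = 6"), with two more leaving because the prescription complicated their cancer treatment.

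**The concern.** A change from v1 to v5 exists only for patients who stay to v5. Here, staying depends partly on tolerating the product and taking it as prescribed, so the comparison is conditioned on something the tablets can influence. Two time points also say little about events that come and go within three months. Percentage change is an awkward measure for a graded scale on which new-onset events start from zero.

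What is at stake is the tolerability comparison between two doses and placebo, in a pilot meant to inform later efficacy studies (section 2.10) and the choice of dosage (section 6). If the stated comparison is followed as written, it describes those who completed the course. The incidence of events among those who started is not named as a comparison.

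**Working it through.** **1. Who can enter the v1-to-v5 contrast.** Inputs from section 5: 31 randomised, 10 dropouts, 21 completers.

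- 31 − 10 = 21, which reproduces the stated number of completers.
- Cross-check with Table 3: the shares of women (62.5%, 33.3%, 85.7%) fit 5/8, 2/6 and 6/7. The total is 13/21 = 61.9%, the figure given in section 5.
- Not able to enter: 10/31 = 32.3%.

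**2. How many left for reasons tied to the product or regimen.** Intervals are Clopper-Pearson 95%.

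- Taste distortion: 6/31 = 19.4% (7.5% to 37.5%), or 6/10 = 60% of dropouts.
- Adding the two who left because of the prescription's burden: 8/31 = 25.8% (11.9% to 44.6%), or 8/10 = 80% of dropouts.
- The text gives no reason for the other 10 − 8 = 2.

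**3. Short events.** This is an illustration. It assumes a 90-day course, random onset, and that only events present on the visit day count. The chance that an event of d days is present at v5 is d/90. At one of v3, v4 or v5 it is 3d/90.

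| Duration (days) | At v5 | At v3, v4 or v5 |
|---|---|---|
| 3 | 3/90 = 3% | 9/90 = 10% |
| 7 | 7/90 = 8% | 21/90 = 23% |
| 14 | 14/90 = 16% | 42/90 = 47% |

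The v5 contrast alone would miss most short events. The diary would record them.

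**4. Percentage change.** On a per-patient reading it is 100 × (grade at v5 − grade at v1) / (grade at v1), which has a zero denominator when the v1 grade is 0. On the other reading, as a change in the percentage of patients affected, it is defined, but it still uses two visits and only patients seen at v5.

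**5. What the diary adds.** It holds dates, intensity and relation to product, so incidence and timing can be derived from it. Its stated comparison, however, is again percentage change between visits. Section 4.2.1 hands out the tolerance and adverse-effect sheets at v1 for return at v3, so the text shows no diary period before v1 to serve as a baseline.

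**6. What is not named.** Neither section 2.8.8 nor section 3.4.7 names on-treatment incidence, worst grade per patient, or stopping because of the product as a between-arm comparison.

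**The case against.** A reader might infer that the plan ignores events between visits and excludes early stoppers from the tolerance analysis altogether. The documents do not support that. The diary runs throughout, is reviewed at every visit and is compared between arms, and CTCAE is also measured at v3 and v4. No passage removes early leavers from those data, and section 2.12 keeps their records. Their loss is certain only for the v1-to-v5 contrast, where it follows from the absent v5 value.

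Four further objections stand, in whole or in part.

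- The reported reasons for leaving were taste distortion and burden. No gastrointestinal dropout is reported, so it is not shown that gastrointestinal events were lost from the comparison. Equally, though, the commonest reason for stopping lies outside the listed gastrointestinal disorders, so neither comparison in section 2.8.8 would show it.
- A reader might infer that a poorly tolerated arm would look clean. That cannot be shown. The dropout split by arm is in a figure not reproduced here, and Table 3 labels its groups by number only.
- Percentage change need not be per patient. Section 2.13 tests percentages by chi-square or Fisher, which fits a change in the share affected. The wording is ambiguous and is undefined on one reading only.
- Nothing calls this contrast the trial's main safety analysis. Section 2.14 dispenses with a data monitoring committee but gives adverse-event evaluation to the medical team.

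It can also be said that safety sets and worst-grade tables belong in an analysis plan. As a general point that is fair. But section 2.8.8 does more than leave the matter open: it fixes a specific comparison, and that comparison is the weak one.

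**Conclusion.** The concern holds for the stated comparison. The CTCAE contrast between arms can include at most 21 of 31 randomised patients. The 10 (32%) it must omit include 6 who stopped because the supplement distorted taste and 2 who stopped because of the prescription's burden. Taken alone it misses events that resolve before v5, and it is undefined from grade 0 if meant per patient. The diary and the v3/v4 visits collect the missing information, but no incidence, worst grade or product-related discontinuation is named as a comparison that would use it.

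This rests on the preliminary counts in section 5, on dropouts having no v5 assessment, and on section 2.12 being followed so that the missing change is not filled in. The size and direction of any bias between arms are unknown. Severity: should-fix, because this is a secondary outcome in a pilot and the data are already collected.

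**What to change.** Reword the comparison in section 2.8.8 along these lines:

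- **Population:** all randomised patients who took at least one tablet.
- **Main tolerance comparison:** number and percent per arm with any event that is new or worse than at v1, from first tablet to last contact, by worst CTCAE grade and by relation to product, using diary and visit data together.
- **Stopping:** number per arm who stopped because of the product, with taste distortion counted, and exact confidence intervals. The question put to leavers under section 2.2 supplies part of this.
- **Visit grades:** keep v1, v3, v4 and v5 as description. If percentage change is retained, say whether it is per patient or a change in the share affected.

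The cost is analysis wording only, since section 3.4.7 already collects dates, intensity and relation to product. The downside is that reported event rates will look less favourable than a v1-to-v5 change among completers.

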#### 2.8.9. General Biochemical Parameters

Biochemical parameters such as cholesterol, albumin, or lymphocytes are general health biomarkers that provide indirect information about nutritional status. They have shown a correlation with body protein, nutrient balance, and energy status [44]. Plasma proteins, mainly albumin and prealbumin, are biomarkers of global protein status. Albumin, a visceral protein, shows a high correlation with mortality and morbidity [83]. Prealbumin, which is more sensitive to protein status changes because it has a short half-life (2–3 days) and hydration status does not affect its concentration [84], will also be measured. Albumin and prealbumin concentrations are considered inflammatory biomarkers associated with nutritional risk [85]. Plasma C-reactive protein (CRP) is an acute-phase protein related to inflammation. The CRP/prealbumin ratio has been proposed as a predictor of mortality and hospital stay extension [86]. A CRP/prealbumin ratio > 0.24 is to be used as a cutoff point [87].

In addition, some vitamins, such as vitamins D, B9, and B12, and minerals, such as iron, zinc, and selenium, are evaluated because they are good biomarkers of nutritional status. Complete blood count and leukocyte differential are evaluated, as well as parameters related to glucose metabolism (glucose, HbA1c, insulin), lipid profile (total cholesterol, HDL, LDL, No-HDL, triglycerides), renal metabolism parameters (creatinine, glomerular filtration rate, urate), biochemistry of anemias (ferritin, vitamin B12, serum folate), proteins (albumin, prealbumin, retinol-binding protein, total proteins), parameters related to hepatic metabolism (bilirubin, alanine aminotransferase-ALAT-), and trace minerals and elements (sodium, potassium, chlorine, calcium) on v1, v3, v4, and v5 to monitor the evolution throughout the study. Changes from the beginning (v1) to the end of the intervention (v5) will be compared between treatments.

#### 2.8.10. Specialized Biochemical Parameters

##### Essential Fatty Acids and Polyunsaturated Fatty Acid Status

Malnutrition occurs frequently in cancer patients due to their oncological process and the treatments received, such as surgery, radiotherapy, or chemotherapy. The status of essential fatty acids (EFAs), linoleic acid (LA) (18:2 *n*-6) and α-linolenic acid (LNA) (18:3 *n*-3), as well as their long-chain polyunsaturated derivatives (LC-PUFAs), especially arachidonic acid (AA) (20:4 *n*-6, eicosapentaenoic acid (EPA) (20:5 *n*-3), docosapentaenoic acid (DPA) (22:5 *n*-3), and docosahexaenoic acid (22:6 *n*-3) (DHA), is essential for cellular homeostasis and, in particular, for the maintenance of immune and anti-inflammatory capacity [88,89,90]. It is well known that the EFA and LC-PUFA profile in erythrocyte membranes provides an accurate estimate of body fatty acid status in both healthy subjects [91] and cancer patients [92,93]. In the latter, EFA and LC-PUFA status is altered, usually due to low EFA intake [94]. The improvement of dysgeusia by the miraculin-based food supplement should potentially lead to increased food intake and, therefore, to a substantial improvement in EFA and LC-PUFA status.

##### Biomarkers of Inflammation (Plasma Cytokines)

Cachectic syndrome, characterized by marked weight loss, anorexia, asthenia, and anemia, is inextricably linked to the presence and growth of the tumor and leads to systemic inflammation and undernutrition due to the induction of anorexia or decreased food intake and increased energy expenditure [95]. Systemic inflammation is a physiopathological characteristic of cancer patients. There are multiple origins of inflammation: tumor cells and activated immune cells release cytokines, chemokines, and other inflammatory mediators. In particular, cytokines play a key role as the main humoral factors involved in cancer cachexia, and a large number of them may be responsible for the metabolic changes associated with cancer wasting [96]. Cytokines, namely, interleukin (IL)-1 and tumor necrosis factor (TNF)-α, have been suggested to be involved in cancer-related anorexia, possibly by increasing the levels of corticotropin-releasing hormone (CRH), a central nervous system neurotransmitter that suppresses food intake, and the firing of glucose-sensitive neurons, which would also decrease food intake. IL-1, in particular, has been associated with the induction of anorexia [9] in that it blocks neuropeptide Y (NPY)-a well-known hypothalamic feeding inductor. In addition, IL-6 increases protein degradation in muscle by activating both the nonlysosomal (proteasome) and lysosomal (cathepsin) proteolytic pathways [97]. Tumor-derived factors, other than cytokines, have been proposed as triggers of the wasting process associated with cancer cachexia. Two of these molecules, lipid-mobilizing factor (LMF) and proteolysis-inducing factor (PIF), have been found in tumor-bearing animals and cancer patients [98]. In addition, alterations in the gut barrier in cancer patients and translocation of bacterial lipopolysaccharide (LPS) can contribute to increased inflammation and production of cytokines and chemokines [99].

##### Oxidative Stress and Antioxidant Defense System (ADS)

Oxidative stress occurs because of an imbalance between the production of free radicals and reactive metabolites and the capacity of the antioxidant defense system (ADS) to scavenge them [100]. Reactive oxygen species (ROS) play important roles in the biology of tumorigenesis. Indeed, ROS represent some of the most relevant carcinogenic entities contributing to the different stages of tumor evolution, acting as inducers of both genomic instability and mediators of signaling pathways related to survival, proliferation, resistance to apoptosis, angiogenesis, and metastasis in preneoplastic and neoplastic cells [101]. ROS are produced mainly in five compartments: mitochondria, cytosol, and single-membrane-bound organelles (peroxisomes, endosomes, and phagosomes) [102], but their major activity lies in the mitochondrion, an organelle responsible for cellular aging and ROS production as a natural byproduct of the electron transport chain (ETC) [101,103]. Under the influence of oncogenes, carcinogenic transformation processes are activated, which results in increased ROS and cellular oxidative stress, culminating in the oxidation of proteins, lipids, and DNA [104]. The role of ROS in the pathological process of cancer transcends all its stages and is relevant in the development of metastasis by increasing the invasion and migration capacity of tumor cells. This is a complex process involving the participation of several proteins and transcription factors [105].

When the hydroxyl free radical (●OH) interacts at the level of the puric bases, a modification occurs at the C8 position of the guanine ring, generating a radical that can be oxidized to 8-hydroxy-2′-deoxyguanosine (8-OHdG) or reduced to 2,6-diamino-4-hydroxy-5-formamidopyrimidine (Fapy G) [106]. These resulting products are highly mutagenic and capable of inducing a G:C to T:A transversion, with 8-OHdG being recognized as an important marker of oxidative DNA damage due to its easy detection [107]. ROS have been described to stimulate the production of R-loops of both DNA and RNA that appear during cell replication conflicts and are important inducers of genomic instability; 8-OHdG has been linked to the production of these fragments [108].

Cells can defend themselves against ROS damage due to the existence of several mitochondrial antioxidant defense mechanisms capable of inhibiting free radical synthesis. Among these mechanisms are enzymatic components such as glutathione peroxidase (GPx), superoxide dismutases (SOD), catalases (CAT) and thioredoxins (Trxs) and nonenzymatic components that are produced endogenously such as glutathione (GSH), lipoic acid, coenzyme Q, and some proteins (ferritin, transferrin, and albumin) [109]. Likewise, the role of exogenous antioxidants present in the diet, such as ascorbic acid, tocopherol (vitamin E), carotenes, and phenolic compounds, stands out [100].

Some of these enzymatic components fulfill their antioxidant functions through actions such as catalysis of the dismutation of O_2_^--^ into H_2_O_2_ and O_2_, converting the effects exerted by SOD into essential processes for all cells exposed to O_2_ [110]. GPx catalyzes the reduction of H_2_O_2_ and organic hydroperoxides in the presence of GSH, acting as a hydrogen donor. During this process, GSH is oxidized to glutathione disulfide (GSSG), which is eventually revitalized by a glutathione reductase enzyme [111]. Other catalysts, such as catalases and the Trx system, are responsible for precipitating the decomposition of H_2_O_2_ into water and O_2_ and for reducing the actions of enzymes involved in the cellular redox balance, respectively [112]. On the other hand, nonenzymatic components of the ADS, such as ascorbic acid and tocopherol, remove free radicals synergistically, with ascorbic acid being necessary to generate reduced tocopherol [113]. Like carotenes, tocopherol exerts antioxidant effects by donating electrons to H_2_O_2_, -OH or O_2_^-^ molecules, thereby inhibiting the formation of ROS in the cytoplasm [114]. Frequently, these antioxidant elements become deficient in cancer cells, facilitating the appearance of oxidative stress and the consequent deterioration of the genetic material together with the promotion of other protumoral phenomena such as resistance to apoptosis or alterations in the regulation of the cell cycle [115]. An emerging model suggests that cancer cells increase the production of ROS to activate localized protumorigenic signaling but balance the increased ROS with elevated antioxidant activity to maintain redox balance [101,103].

##### Plasma Metabolomics

Cancer has multiple effects on metabolism that include both rewiring of intracellular metabolism to allow cancer cells to proliferate inappropriately and adapt to the tumor microenvironment and changes in normal tissue metabolism. Metabolomics is a term used for the systematic identification and quantitation of all the metabolic products of a cell, tissue, body fluid, organ, or organism under varying conditions. Indeed, the metabolome of plasma is a dynamic collection of metabolites that represent its net response to current conditions [116]. Metabolomics techniques are used to study metabolic shifts, including changes in metabolite concentrations and disturbed metabolic pathways, in the progression of cancer cachexia and expand the fundamental understanding of muscle loss [117]. In particular, the abundance of paraxanthine is decreased in cancer cachexia patients compared to those without cachexia. These patients undergo radical treatments with radio-/chemotherapy, and high 3-hydroxybutyrate levels are detected at an early stage of the treatment in patients affected by head and neck squamous cell carcinoma cancer. Thus, 3-hydroxybutyrate could be exploited as a fast and sensitive biomarker of malnutrition or cachexia [118]. Overall, 45 metabolites and 18 metabolic pathways have been reported to be associated with cancer cachexia. Using random forest analysis, 15 of these metabolites have been identified as highly discriminating between disease states; within those metabolites, carnosine, leucine, and phenylacetate have been validated [119].

##### Oral and Intestinal Microbiota and Metagenomics

The microbiota or microbiome refers to all microbial organisms that naturally exist within an ecosystem, i.e., part of an organism such as the oral cavity, the intestine, or the vagina. The concept of the microbiome refers not only to the members of the microbial ecosystem but also encompasses their collective functional capacity (metagenome) and activity (metabolome), including interactions within the community and with the host. Indeed, the metagenome is a term used to design the collective genome representative of the many microorganisms existing in a particular ecosystem, and metagenomics is the systematic study of the assemblages of genomes for those microorganisms.

Currently, much attention has been given to the oral microbiome and oral and systemic health [120]. The mouth has a variety of microbes second only to the gut in the complexity of human sites. Differences in the oral microbiome occur with old age, which may be due to oral conditions and diseases, e.g., cancer and other chronic diseases [121]. Many factors contribute to the salivary microbiome profile. In particular, radiotherapy for the treatment of head and neck cancer can cause tissue damage and specifically the salivary glands, causing an alteration in the composition of saliva accompanied by dermatitis, oral mucositis, xerostomia, dysgeusia, dysphagia, and dysbiosis [122]. The latter is related to changes in the quantitative and qualitative composition of the microbiota, mainly increased cariogenic cocci and yeast populations [123]. These changes may lead to altered host–microbe interactions or homeostatic imbalance that can contribute to a disease state, often with inflammation [124]. Recently, the oral microbiome has been suggested to be an explanatory factor for nasopharyngeal carcinoma prognosis. Lower within-community diversity is associated with higher mortality, and certain measures of between-community diversity are related to mortality [125]. Additionally, recent data suggest a potential association of the oral microbiome with mutational changes in oral squamous cell carcinoma [126]. Therefore, modifications in oral biofilms of irradiated patients improving dysgeusia, such as treatment with miraculin, could contribute to better oral health.

Current scientific evidence supports the finding that the composition and modification of the gut microbiome play an important role in the development of many different types of cancer. As an example, alterations in the oral, fecal, and pancreatic microbiome composition have been associated with the etiology and progression of pancreatic ductal adenocarcinoma [127]. Metagenomic studies have reported that the intestinal microbiota can affect not only carcinogenesis but also cancer prevention and that microbes may act through various mechanisms sometimes opposite to each other (e.g., microorganisms are capable of acting as tumor suppressors or, conversely, as oncogenic), giving rise to a complex and bidirectional relationship [128,129]. The gut microbiota has also been found to be associated with extragastrointestinal tumors, such as breast cancer, leukemia, and lung cancer [130]. The intake of the miraculin-based food supplement, particularly in several cancers, e.g., head and neck cancer, would ameliorate dysgeusia and food intake, which in turn could contribute to the improvement of intestinal dysbiosis in cancer patients treated with radiotherapy.

